**Week 6**

(Follow-up Anoscopy, HPV genotyping )

# OBJECTIVES

## Primary Objectives

- - 1. To evaluate the safety and tolerability of intra-anal administration of Artesunate, administered via suppository with 3 different schedules, in patients with high-grade anal intraepithelial neoplasia (AIN 2/3).]

## Secondary Objectives

- - 1. To measure the effect of intra-anal topical Artesunate administration determined by pathology, based on the regression of AIN2/3 at study weeks 16, 28, and 40. Regression defined as either AIN1 or no AIN lesion detected by HRA/biopsy and anal cytology.
    2. To evaluate the clearance of HPV as assessed by HPV genotype testing of cytologic specimens.

1.2.3 To create a tissue bank for future studies.

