**Week 28**

Assess for residual disease: HRA + biopsy + pap smear + HPV genotyping

No detection of AIN2/3 lesion by biopsy + anal pap smear

Detection of AIN2/3 lesion by biopsy + anal pap smear

Ablation in OR***

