**Week 40**

Assess for relapsing disease: pap smear and if clinically indicated HRA + biopsy + HPV genotyping

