## Noninvasive topical therapy for anal dysplasia

Current available off-label topical treatment options include Imiquimod and 5-fluorouracil. Curative rates with these topical agents is poor, with complete reponse rates of 17% in patients using 5-fluorouracil and 24% patients using Imiquimod. Recurrence rates are high—58% in 5-fluorouracil users and 71% in Imiquimod users. Forty-three percent of imiquimod users and 27% in the 5-fluorouracil users experience grade 3-4 toxicities, leading to poor compliance rates.

The development of an effective topical therapy for preinvasive AIN2/3 lesions that could be self- administered would be a game-changing innovative treatment option for patients with preinvasive HPV disease. A topical treatment option would decrease adverse sequelae related to ablative procedures, decrease visits to specialized healthcare providers, and result in considerably decreased healthcare costs. In addition, in many cultures, HPV disease, carries a social stigma.[12](#_ENREF_12) The development of a topical therapy that could potentially be self-administered, would be empowering for patients with preinvasive lesions. A topical therapeutic also has the potential to obviate the need for surgery.

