## Analysis of Primary and Secondary Endpoints

- - 1. Analysis of safety endpoints

The NCI common terminology criteria for adverse events (AE) (CTCAE 4.0) will be used to evaluate toxicity. We will consider a toxicity to be an adverse event that is possibly, probably or definitely related to treatment. The maximum grade of toxicity for each category of interest will be recorded for each patient, and the summary results will be tabulated by category, grade, and dose level. Serious (≥ Grade 3) toxicities will be described on a patient-by-patient basis and will include any relevant baseline data.

Once the MTD (or RP2D) is found, then secondary outcomes will be evaluated based on MTD.

- - 1. Analysis of secondary efficacy endpoints

Regression of AIN 2/3 to either AIN 1 or the absence of AIN will be used as dichotomous variables and the proportion of patients with the characteristics and the corresponding 95% confidence intervals will be calculated.

HPV viral genotype will be collected longitudinally over time as a qualitative measure.

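### Week 40 is listed as a regression time point, but under the schema it can show only relapse or the effect of ablation, and the planned proportion separates neither

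*Protocol*

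**What the plan says.** - **Objective (Synopsis and 1.2).** The effect is determined by pathology, "based on the regression of AIN2/3 at study weeks 16, 28, and 40". The definition reads: "Regression defined as either AIN1 or no AIN lesion detected by HRA/biopsy and anal cytology". Week 40 has the same standing as weeks 16 and 28.
- **Schema (after the Synopsis, repeated in section 7).** Week 28 is to "Assess for residual disease: HRA + biopsy + pap smear + HPV genotyping", and week 16 has the same purpose. The week 16 box separates patients with some improvement from those with none and shows ablation. The week 28 box splits on "detection of AIN2/3 lesion by biopsy + anal pap smear" and again shows ablation. Week 40 reads differently: "Assess for relapsing disease: pap smear and if clinically indicated HRA + biopsy + HPV genotyping".
- **8.3.8.** Residual disease seen by HRA at week 16 or week 28 leads to ablation. There is no exception for partial improvement.
- **Week 40 procedures elsewhere.** The Synopsis schedules HRA and biopsy at weeks 16, 28 and 40. Section 8.3.7 and the Appendix A calendar schedule HRA at week 40. None of the three attaches a condition.
- **Analysis.** Section 14.3 states: "Regression of AIN 2/3 to either AIN 1 or the absence of AIN will be used as dichotomous variables", reported as a proportion with a 95% confidence interval. The Synopsis says the same. Section 10.1 adds a comparison of changes from baseline to weeks 16, 28 and 40 with a clinic database.
- No objective, endpoint or analysis defines relapse or duration of response, or says how ablated patients count at later visits.

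**The concern.** Week 28 sorts patients by whether AIN2/3 is present. Those who go on without ablation are already regressed by the protocol's own definition, so at week 40 they can only stay clear or relapse. Patients who become newly clear at week 40 are those who were ablated. A week 40 regression proportion that does not set ablated patients apart could therefore credit artesunate with the effect of surgery, and it could hide relapse among responders.

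Recurrence is part of the protocol's case for a new treatment. Sections 2.1 and 2.2 cite up to 50% and 68% after ablation, and "58% in 5-fluorouracil users and 71% in Imiquimod users" for the topical agents. The database in 10.1 consists of patients treated with HRA and ablation. If ablated trial patients count as regressed at week 40, that comparison partly sets ablation against ablation.

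**Working it through.** The protocol states no rate, power or sample size for regression or relapse, so there is no figure to reproduce. The check follows patients through the schema and then uses illustrative counts. The cohort size of 12 is the MTD cohort total in 14.1. All response counts are assumptions. Intervals are exact (Clopper-Pearson).

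**1. Who can newly regress at week 40.** The arrows of the schema are not reproduced in the text, so this reading rests on the box contents. It also assumes that ablation takes place before the week 40 visit.
- AIN2/3 at week 28: ablated. Clearance at week 40 reflects ablation.
- No AIN2/3 at week 28: already regressed. At week 40 the patient is still clear or has relapsed.

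Neither group can contribute a new regression due to artesunate alone.

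**2. Week 28 to week 40.** Let 6 of 12 be clear at week 28 and the other 6 be ablated. Let k be the responders who relapse and a the ablated patients who are clear at week 40. The week 40 proportion is:
- (6 − k + a)/12 as observed;
- (6 − k)/12 if ablated patients count as not regressed;
- (6 − k)/6 if ablated patients are excluded.

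With k = 3 and a = 6:
- as observed, 9/12 = 75% (42.8% to 94.5%);
- ablated as not regressed, 3/12 = 25% (5.5% to 57.2%);
- ablated excluded, 3/6 = 50% (11.8% to 88.2%).

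The first figure is above the 6/12 at week 28 although half the responders relapsed. The same 9/12 arises with k = 0 and a = 3, so the observed proportion does not distinguish no relapse from 50% relapse.

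**3. Week 16 to week 28.** Count ablated patients as not regressed. With R16 and R28 patients clear at the two visits:

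relapses = R16 − R28 + late regressors

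Late regressors can come only from patients who still had AIN2/3 at week 16 and were not ablated.
- *If the schema's partial-improvement branch governs:* the general bounds on relapses are max(0, R16 − R28) and min(R16, 12 − R28). For 6/12 at both visits they are 0 and min(6, 6) = 6. Each visit reads 50% (21.1% to 78.9%), while relapse among the 6 responders could be anything from 0/6 (0% to 45.9%) to 6/6 (54.1% to 100%). The upper end needs all 6 non-responders to stay unablated and later regress.
- *If 8.3.8 governs:* patients with visible residual disease at week 16 are ablated. Late regressors are then close to nil, relapses are about R16 − R28, and the mixing largely disappears.

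**4. The proposed measures on the example in step 2.** Assume the 6 week 28 responders were never ablated and all 12 have a week 40 status.
- Sustained without ablation: 3/12 = 25% (5.5% to 57.2%).
- Relapse among responders: 3/6 = 50% (11.8% to 88.2%).

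Neither depends on a, the number cleared by ablation.

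**5. Whether week 40 status is known.** The regression definition calls for HRA/biopsy and cytology. The schema guarantees only a pap smear at week 40. The Synopsis, 8.3.7 and Appendix A schedule HRA for everyone, and the Synopsis also biopsy.

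**The case against.** - **Regression is a status, not a transition.** A patient clear at week 40 is in regression at week 40, and one visit can serve both purposes. This is fair: the difference in labels alone is a mild conflict. What remains is that one proportion cannot serve both purposes once ablated patients are in it.
- **A counting rule would be enough for weeks 28 to 40.** If ablated patients count as not regressed and everyone is examined, the fall from week 28 to week 40 equals the relapses, and the week 40 proportion equals sustained regression from week 28. This is correct, but the protocol states no such rule. It also leaves weeks 16 to 28 open if the partial-improvement branch applies.
- **The SAP may define relapse.** It may, and the absence of a relapse definition alone would be no finding. The mismatch between the objective and the schema lies in the protocol itself, and 14.3 fixes the quantity. Section 14.3 names no visit; reading it visit by visit is inferred from 1.2 and 10.1.
- **Durability is not an objective.** True. The protocol also argues from morbidity, low response rates and toxicity. It does, however, devote the week 40 schema visit to relapse.

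Three stronger readings are tempting. A reader might infer that the trial cannot learn about relapse at all. But study visit data go into a database (10.1) and nothing forbids cross-tabulation; the limit is in the planned summaries. A reader might infer that every patient already has the paired assessments. The schema's conditional week 40 HRA and biopsy rule that out. A reader might apply the range of 0/6 to 6/6 to week 40. It concerns weeks 16 to 28, and only under one of two conflicting passages.

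**Conclusion.** The point holds in a limited form. If the schema is followed, week 40 cannot show new regression due to artesunate, and the planned proportion neither separates ablated patients nor shows relapse among responders. In the 12-patient illustration the week 40 result is 75%, 25% or 50% for the same patients, depending on a rule the protocol does not give. The further ambiguity between weeks 16 and 28 (0 to 6 of 6 responders relapsing behind 6/12 at both visits) depends on whether the schema or 8.3.8 governs at week 16.

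The counts are illustrative, and the conclusion assumes that patients follow the schema and are ablated before week 40. The endpoint is secondary and descriptive, so this is an inexpensive improvement. It does not touch the dose-finding objective.

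**What to change.** In the Synopsis, 1.2 and 14.3, keep regression at weeks 16 and 28 and replace regression at week 40 with two patient-level measures:
- (a) regression sustained to week 40 without ablation, over all treated patients, with ablated patients counted as not sustained;
- (b) relapse, meaning AIN2/3 found again at week 28 or 40, among earlier responders not ablated in between.

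Report both as counts with exact 95% confidence intervals. State also how patients ablated after week 16 count at week 28.

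Two sets of passages must be reconciled first. One is the week 16 branch for partial improvement in the schema against 8.3.8. The other is the conditional week 40 HRA and biopsy in both copies of the schema against the unconditional HRA in the Synopsis, 8.3.7 and Appendix A (with biopsy in the Synopsis). Both measures need week 40 AIN2/3 status.

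The cost is wording and that reconciliation. No visit is added. If the schema's condition stands, some patients will lack the week 40 status that the measures need. The relapse denominator is responders only, so its interval will be wide, as 3/6 shows.

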# BACKGROUND

## HPV-associated malignancies of the anus

Virtually all anal squamous cell cancers (ASCC) are caused by human papillomavirus (HPV). Exposure to HPV occurs with the onset of sexual activity. While most people clear their infection without intervention, and without sequelae, a subset does not. Persistent infection with a high-risk HPV type (most commonly types 16 and 18) is the most common cause of ASCC as well as anal precursor intraepithelial lesions, anal intraepithelial neoplasia (AIN2/3). Additional factors contribute to the development of ASCC, since viral integration into the host genome is necessary but not sufficient for the initiation and persistence of malignant transformation. Currently, there are no available treatments that can eradicate HPV infection. Successful prevention of ASCC in infected individuals is based on early detection of preinvasive lesions prior to the development of cancer.

Although preventative vaccines that protect against infection with HPV types 16 and 18 have been introduced for preteen and teenage girls and boys since 2006, the rates of vaccination have remained low in the United States. Recent data indicate that the rate of preventive vaccination in eligible girls, in 2012, was only 33%.[9](#_ENREF_9) The impact of HPV vaccination is yet to be determined, given the young age of vaccine administration and the long time interval in which anal cells transform through the anal dysplasia-carcinoma sequence.

Despite the availability of several, inexpensive, noninvasive screening strategies to detect precursor lesions, the incidence of HPV disease (ASCC and AIN 2/3) in patients remains high. In human immunodeficiency virus (HIV)-seropositive persons, the incidence of anal cancer has increased exponentially over the past few decades, making it one of the most common HIV-associated cancers.

The primary strategy to decrease disease burden in HPV-infected individuals is to intervene when premalignant anal disease, AIN2/3, is detected prior to the development of ASCC. All treatments for AIN2/3 are ablative and include electrocauterization/fulguration, hyfrecation, laser vaporization. Because they involve tissue destruction, all current therapeutic options have the potential for adverse sequelae, such as pain, fecal incontinence, and anal stenosis. Furthermore, these ablative techniques are not curative. Recurrences are common; in HIV-seronegative persons treated with ablation, recurrence is as high as 50% within one year of ablation.[2](#_ENREF_2) In HIV-positive individuals, recurrence rates are as high as 68%.[10](#_ENREF_10) An effective topical intervention that targets the underlying cause, HPV, would obviate the need for surgery and prevent progression to ASCC.

## Noninvasive topical therapy for anal dysplasia

Current available off-label topical treatment options include Imiquimod and 5-fluorouracil. Curative rates with these topical agents is poor, with complete reponse rates of 17% in patients using 5-fluorouracil and 24% patients using Imiquimod. Recurrence rates are high—58% in 5-fluorouracil users and 71% in Imiquimod users. Forty-three percent of imiquimod users and 27% in the 5-fluorouracil users experience grade 3-4 toxicities, leading to poor compliance rates.

The development of an effective topical therapy for preinvasive AIN2/3 lesions that could be self- administered would be a game-changing innovative treatment option for patients with preinvasive HPV disease. A topical treatment option would decrease adverse sequelae related to ablative procedures, decrease visits to specialized healthcare providers, and result in considerably decreased healthcare costs. In addition, in many cultures, HPV disease, carries a social stigma.[12](#_ENREF_12) The development of a topical therapy that could potentially be self-administered, would be empowering for patients with preinvasive lesions. A topical therapeutic also has the potential to obviate the need for surgery.

## Artesunate

Artesunate is a semisynthetic derivative of artemisinin, a plant compound extracted from the leaves of sweet wormwood, *Artemisia annua,* an herb used in Chinese traditional medicine for antimalarial treatment for over two thousand years, with marketed formulations since the late 1980s.[13](#_ENREF_13)

The safety profile of Artesunate and related compounds has been established based on millions of malaria patients, ranging from infants to adults, over decades.[14](#_ENREF_14) Artesunate has been shown to be safe and well-tolerated when administered orally, intravenously, intramuscularly, or intra- rectally, as a suppository.[15-19](#_ENREF_15) Reports submitted to the FDA by both the WHO and by Novartis summarize many of the safety studies (see Section 2.4) conducted with artemisinin and its derivatives, including artesunate.

Recently, Artesunate compounds have been shown to have antitumor activity against several human solid tumor cell lines, including breast, colon, ovarian, prostate, renal, and non-small cell lung cancer.[18](#_ENREF_18) Of particular relevance, artemisinin derivatives have also been shown to have a cytotoxic effect on HPV-immortalized epithelial cells.[18](#_ENREF_18)

Artemisinin and its derivatives, including Artesunate, have been shown to decrease cell proliferation, reduce angiogenesis and trigger apoptosis in cancer cells. Although the mechanisms of action are not completely understood, in human solid cancers, sensitivity to Artesunate has been reported to be associated with expression of angiogenesis-related gene transcripts.[23](#_ENREF_23) Tumor susceptibility has also been reported to be correlated with cell surface overexpression of transferrin receptor [24](#_ENREF_24) and with intracellular ferrous iron.[6](#_ENREF_6) It has been demonstrated that artemisinin and its derivatives contain an endoperoxide bridge that reacts with intracellular ferrous iron to generate free radicals, leading to cell death.[15](#_ENREF_15)

## Study Drug Rationale

As with cervical squamous cell cancer and cervical intraepithelial neoplasia, both ASCC and AIN2/3 are associated with functionally obligate expression of two viral proteins, E6 and E7.[25](#_ENREF_25) Epithelial cells that express either or both of these oncoproteins also overexpress the transferrin receptor, and have increased levels of intracellular iron, compared to normal cells.

Because cervical squamous cell cancers and their precursors, intraepithelial lesions, overexpress the transferrin receptor,[23](#_ENREF_23) these observations prompted a subsequent study of the cytotoxic effect of dihydroartemisinin (DHA), the bioactive form of Artesunate, on papillomavirus-expressing epithelial cells.[5](#_ENREF_5) *In vitro* studies demonstrated that, while DHA had little effect on normal cervical epithelial cells, it had a significant cytotoxic effect on HPV-immortalized cervical cells.[5](#_ENREF_5) In addition, formulated as a local treatment (2.22 mg DHA dissolve in 100 µl dimethylsulfoxide) in an oral mucosal canine nonclinical model which has 100% known tumor growth rate with HPV-infection, DHA has been reported to inhibit papillomavirus-induced tumor formation. In addition, tumor-negative dogs developed antibodies against the HPV L1 capsid protein.[5](#_ENREF_5)

Together, these findings suggest that topical administration of an Artesunate compound may provide therapeutic benefit for intraepithelial HPV disease. Given the unmet need for a local treatment for AIN2/3 lesions and that Artesunate has demonstrated a favorable safety profile for decades in both children and adults, we designed a prospective, dose-escalation, Phase 1 study of an Artesunate suppository, administered intra-anally, to non-invasively treat AIN2/3 lesions.

## Study Drug Dosing Rationale

- - 1. **Single Dose Toxicity**

The LD50 (lethal dose that kills 50 percent of the test sample) of Artesunate, given as intravenous and intramuscular injections to mice were determined as 699 mg/kg and 475 mg/kg, respectively. Reduced appetite and emesis were the only clinical symptoms reported with a rising dosing schedule in dogs of 37 mg/kg on day 1, 75 mg/kg on day 2, and 150/kg on day 3. Maximal tolerated doses in monkeys were 60 mg/kg and lethal doses were found to be 160 mg/kg. The adverse effects observed were central nervous system effects (depression, unstable gait, tremor, and convulsion) and respiratory depression. In the oral formulation, dogs have tolerated doses of up to 120 mg/kg with some liver damage at this concentration or higher.[14](#_ENREF_14)

- - 1. **Repeated Dose Toxicity**

In repeated dose-toxicity studies, intravenous administration of artesunate into canines, at doses of 10 and 40 mg/kg for 14 days, did not produce clinical symptoms or significant hematological, biochemical, or histopathological changes. Monkeys who were given daily doses of 10 and 32 mg/kg daily intravenous injections for 14 days did not experience adverse effects.[14](#_ENREF_14)

- - 1. **Organ Toxicity**

No artemisinin-induced embryotoxicity has been reported in humans.[26](#_ENREF_26) Neurotoxicity-associated with artemisinins appears to be not only dependent on dose but also on the route of administration and the type of artemisinin derivative. Water-soluble artesunate shows markedly less neurotoxicity in laboratory animals than oil-soluble arteether and artemether.[26](#_ENREF_26) In mice, neurotoxic effects of artesunate in a 28-day oral dosing schedule were observed at a dose of >200 mg/day.[27](#_ENREF_27)

- - 1. **Dosing rationale**

In summary, local tissue application in canine models infected with oral mucosal HPV-derived tumors of a dose of 2.22 mg resulted in an absence of tumor formation. This dosage is significantly less than the first-line 10 mg/kg anti-malarial rectal suppository dosing administered to young children and the 200 mg suppository available for adults (4 mg/kg for a 50-kg individual). No serious adverse events are anticipated at the proposed dose escalation levels of 200 mg (4 mg/kg for a 50-kg adult), 400 mg (8 mg/kg for a 50-kg adult), and 600 mg (12 mg/kg for a 50-kg adult). A five-day daily dosing schedule is selected based on the clinical toxicology and pharmacology literature of anti-malarial and cancer trials.

We anticipate that this Phase I dose escalation trial of intra-anal suppository administration will achieve local tissue drug concentrations adequate to achieve cytotoxicity of HPV-infected dysplastic cells.

# PATIENT SELECTION

## Eligibility Criteria

- Age ≥ 18 years.
- Biopsy-confirmed high-grade anal dysplasia (AIN 2, AIN 3, HSIL) by HRA. This includes patients who are newly diagnosed with AIN 2/3 as well as those who have recurrent AIN 2/3 after medical therapy or surgical therapy.
- Female of childbearing potential: negative urine pregnancy test.
- Adequate contraceptive use for males and females of reproductive potential.
- Able to provide informed consent.
- Patients who have the ability to collaborate with planned follow-up (transportation, compliance history, etc.).
- Patient who have and have not been immunized with the HPV vaccine.
- Weight ≥ 50 kg.
- Life expectancy > 2 years.

